### Statistical Methodology

An a priori computation of the required sample size based on the type of test, the expected effect size, the type I and type II error rates, the number of groups, and the number of measurements were performed according to Lu et al [41]. The statistical power analysis was conducted for a mixed model of repeated measures for 2 groups, 1 measure at a time (corresponding to the main cognitive performance scores detailed) with a 0.7 pre-post correlation, a 20% dropout rate, a medium effect size (0.5), a significance level of α=.05, and a statistical power of 1–β=.80. The necessary sample size for these parameters was 77 (n=154) participants per group.

The MUL stored the personal data of the interested and eligible participants on an internal cloud service, protected from external access. The data set for statistical analysis was fully anonymized. All data storage and processing comply with the General Data Protection Regulation (GDPR) and other applicable regulations. Where possible, fully anonymized data may be made publicly available through open-access repositories supporting the Open Science Initiative.

## Results

### Participant Flow

The project received funds from June 1, 2021, to October 31, 2023. The study’s design, management, analysis, and reporting are independent of the funder. The study, from recruitment to completion of follow-up, was planned to take place from January 2022 to May 2023. The recruitment phase was performed from January 2022 to mid-January 2023. As shown in Figure 9, a total of 310 participants were tested for eligibility and 122 were excluded because of not meeting the inclusion criteria. The most common cause of exclusion was the MoCA score being below 26 points, suggesting the presence of objective cognitive impairment. The recruitment rate (61%, 188/310) was acceptable. Following this, 188 participants were allocated to an experimental group (n=100, 53.2%) or a control group (n=88, 46.8%), with an allocation ratio of 1:0.88.

**Figure 9 figure9:**
[figure not shown]
CoSoPhy FX (Cognitive, Social, and Physical Effects) study flowchart. Study design: a randomized, parallel-group, 2-arm, superiority study; allocation ratio: 1:0.88; population: individuals aged 65-85 years; location: Poland; time frame: 3 months.

In the experimental group, 20 participants declined to participate before the start of the intervention and withdrew their consent without giving a reason. A total of 12 participants withdrew because they reported somatic and mental health problems unrelated to the intervention. In the experimental group, 68 participants completed the intervention.

In the control group, 22 participants declined to participate before the start of the intervention and withdrew their consent without giving a reason. A total of 4 participants withdrew because they reported somatic and mental health problems unrelated to the intervention. In the control group, 62 participants completed the intervention. There were no missing data.

The data are currently being analyzed, and we plan to publish the results by the end of September 2024.

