**Figure 8 figure8:**
[figure not shown]
Memory exercise.

The targeted sample size was 200 participants, equally divided between the experimental and the control groups. Both groups were balanced regarding sex.

The experimental group members underwent a 3-month computerized VR dual-task training program, as described. The control group passively experienced 360° photographs and videos from natural environments without dual-task physical and cognitive training. This technique is frequently used in cognitive studies, offering a passive experience devoid of cognitive challenges [28]. In both groups, the participants were encouraged to use the VR-HMD for a minimum of 3 sessions of 12 minutes per week for 3 months, that is, for at least 36 sessions in total.

The first training session occurred at the MUL, where the participants were trained on how to use the VR-HMD. At the end of the session, the participants took the VR-HMD to their homes to use them according to the schedule described.

The adverse effects of using VR headsets, often referred to as cybersickness, have been reported to include eye strain, dizziness, nausea, and vomiting [29]. However, these side effects are most often due to suboptimal use of the technology, for example, by using VR content with quick changes of position, low image resolution, and low display refresh rates. The VR app used in the study was designed specifically for older adults and avoided any such drastic camera movements.

The app used in the control group had previously been tested by older adults in 15 older adult care homes in Switzerland and Finland. The first version of the app, containing cognitive training, used in the experimental group was tested by 30 older adults in usability studies by terzStiftung in Switzerland between September 2021 and January 2022. After 8 workshops, the feedback was used to develop updated versions of the app. The resulting cognitive training program, image quality, and usability were rated as high by the participants [30]. The results confirm that VR-HMDs are safe for use by high-functioning healthy older adults at home without substantial risks or side effects.

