Nevertheless, participants received explicit instructions to discontinue the VR intervention and contact the researchers if they experienced any side effects. Moreover, in the case of suspected side effects, the participants would be withdrawn from the study, and this would be reported as an adverse event. Any side effects could be reported through a software app running on their mobile phone, tablet, or computer. At the end of the intervention, an open-ended questionnaire was used to collect feedback, including information on perceived side effects.

To acquire reliable and comprehensive outcome data, strategies were used to promote participant retention and ensure follow-up completion (Textbox 2). If participants discontinued the intervention or deviated from the protocol, information regarding their decision was collected with various self-reported outcome data related to their experience, expectations, perceived benefits, and any changes observed during their participation.

Promoting participant retention and ensuring follow-up completion.

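### Health-related withdrawals were numerically more frequent in the VR training arm (12/80 against 4/66); all are labelled unrelated, so the stated adverse-event route would leave them out of the safety comparison still to come

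*Protocol article*

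**What the plan says.** **Withdrawals (Results, Participant Flow).** The article reports that "188 participants were allocated to an experimental group (n=100, 53.2%) or a control group (n=88, 46.8%), with an allocation ratio of 1:0.88". For the training arm it then says "In the experimental group, 20 participants declined to participate before the start of the intervention and withdrew their consent without giving a reason", followed by "A total of 12 participants withdrew because they reported somatic and mental health problems unrelated to the intervention" and "In the experimental group, 68 participants completed the intervention". For the control arm, 22 declined before the start, "A total of 4 participants withdrew because they reported somatic and mental health problems unrelated to the intervention", and 62 completed. The text around the flowchart does not describe the health problems further.

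**Adverse events (Methods, Intervention).** The rule given is that "in the case of suspected side effects, the participants would be withdrawn from the study, and this would be reported as an adverse event". Participants were told to stop and contact the researchers if they had side effects, and could report them through an app. In addition, "At the end of the intervention, an open-ended questionnaire was used to collect feedback, including information on perceived side effects". The same section says that information was collected from those who discontinued or deviated.

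**Safety statement (Methods, Intervention).** After describing tests of the control app in 15 care homes and usability studies of a first version of the training app in 30 older adults, the article concludes: "The results confirm that VR-HMDs are safe for use by high-functioning healthy older adults at home without substantial risks or side effects".

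**Status.** The trial data are described as still under analysis. The article gives no adverse-event count.

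**The concern.** A randomised control group allows harms to be compared without deciding, case by case, what caused each one. If events are first sorted by attributed cause and only those thought to be related are counted, that advantage is lost. Here the stated route to an adverse event runs through suspicion of a side effect, and every health-related withdrawal in both arms carries the label unrelated. Taken together, the two passages send all 16 outside the adverse-event count.

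This matters more because the counts lean towards the training arm. Both arms wore a headset, so effects common to headsets would be expected in both. What differs is the active upper-body and cognitive training, and the headset model. An excess in the training arm bears on those differences, and only a comparison by arm can show it. The symptoms that the article lists for headset use, such as eye strain, dizziness and nausea, are also somatic complaints, so a reader cannot separate them from a category described only as somatic and mental health problems.

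The safety statement adds to this. It treats home safety as settled before the trial's own data are reported. Yet the Challenges section gives the risk of falling among the reasons for changing the intervention, the Discussion lists falls and cybersickness as risks, and the Limitations name cybersickness as something that may affect adherence.

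**Working it through.** **Inputs (Results, Participant Flow).** Allocated: 100 and 88. Declined before start: 20 and 22. Health-related withdrawals: 12 and 4. Completers: 68 and 62.

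**1. Reproduce the article's completers.**
- Training: 100 − 20 − 12 = 68, as stated.
- Control: 88 − 22 − 4 = 62, as stated.

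The flow closes exactly in both arms.

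**2. Denominators.** The article does not state how many started. Removing the pre-start refusals gives 100 − 20 = 80 and 88 − 22 = 66. This reading assumes that the 12 and 4 left after starting, which the text implies but does not say outright. All randomised (100 and 88) is the check.

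**3. Risks and risk ratio.** The standard error of log RR is √(1/a − 1/n₁ + 1/b − 1/n₂).
- Derived starters: 12/80 = 15.0%; 4/66 = 6.1%; RR = 0.150/0.0606 = 2.48. The standard error is √(1/12 − 1/80 + 1/4 − 1/66) = 0.553, so the 95% CI is exp(0.906 ± 1.96 × 0.553) = 0.84 to 7.31.
- All randomised: 12/100 = 12.0%; 4/88 = 4.5%; RR = 2.64, 95% CI 0.88 to 7.89.

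**4. Risk difference.**
- Derived starters: 15.0 − 6.1 = 8.9 points. The 95% CI is −1.6 to 19.0 by Newcombe's method and −0.8 to 18.7 by Wald.
- All randomised: 12.0 − 4.5 = 7.5 points, Wald 95% CI −0.3 to 15.2.

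**5. Test and power.** Fisher's exact p = 0.11 on either denominator. On the derived starters, Pearson chi-square gives p = 0.085 and Barnard's test p = 0.10. Power to detect true rates of 15.0% and 6.1% with 80 and 66 people is about 40%, so a non-significant test is weak reassurance.

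**6. What a test in 30 users can support.** The article gives no event count for the usability studies. Assume the most favourable count, zero. The one-sided 95% upper bound on the true rate is then 1 − 0.05^(1/30) = 9.5%. Any count above zero raises that bound, so 9.5% is the least it can be. A rate of several per cent is therefore not excluded.

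**7. The two passages side by side.** Intervention: suspected side effect → withdrawal → adverse event. Participant Flow: 16 health withdrawals, all unrelated. No other route to an adverse event is stated. Adverse events arising from these 16 under the text as written: 0 in each arm.

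**The case against.** **No harm signal has been lost.** A reader might infer that a signal has been dropped from the safety result. The documents do not support that: the article contains no safety result, the analysis is under way, and both counts are openly given by arm. This stands. The point concerns what the stated route would produce in the later report.

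**The arms are not shown to differ.** Every interval includes no difference, and total attrition is similar: 32/100 (32.0%) against 26/88 (29.5%). This also stands. The excess is numerical only. Low power means that a difference is not excluded; it does not establish one.

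**The rule does not say only.** The Intervention section says that suspected side effects are reported as adverse events, not that nothing else is. That is fair, and the full protocol may say more. But it is the one route the article describes, and the label in Participant Flow places all 16 outside it.

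**Non-completers were not out of reach.** App reporting, contact with the researchers, follow-up of people training less than three times a week and information taken at discontinuation all extend beyond completers. This stands, so capture of side effects cannot be said to rest on the final questionnaire. It also means that the material for a better table should exist.

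**The 12 may well have been unrelated.** Nothing in the documents shows that any withdrawal was mislabelled, and overlap between somatic complaints and headset symptoms is no evidence of it. How relatedness was judged is detail that an article can leave to the full protocol, and no fault is claimed there.

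**Risks are acknowledged elsewhere.** The Discussion is candid about falls and cybersickness. That is to the authors' credit, but it makes the claim of confirmed safety harder to reconcile with the rest of the article.

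**Conclusion.** The point holds as a reporting weakness that can still be corrected. Health-related withdrawals were numerically higher with VR training: 15.0% against 6.1%, RR 2.5 (95% CI 0.8 to 7.3). The data fit chance, and they also fit a several-fold increase. With all 16 labelled unrelated and suspected side effects the only stated route to an adverse event, an adverse-event comparison built on the text would contain none of them.

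The ratio rests on derived denominators of 80 and 66; all randomised gives 2.6, so the conclusion does not depend on that choice. It does not establish that the training caused harm, that the withdrawals were misclassified or that results were withheld.

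The safety statement under Intervention is too strong for its basis, which for the training app is usability work on a first, later updated version in 30 people.

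**What to change.** 1. In the safety analysis, tabulate all health-related withdrawals and events by arm regardless of attributed cause, with the risk difference and its 95% confidence interval. Draw on the information already collected at discontinuation as well as the app reports and the final questionnaire. Show somatic and mental problems separately, and give relatedness as a secondary column, not as a condition for entering the table.
2. State the denominator, and show the result for all randomised alongside that for those who started.
3. In the Intervention section, replace the claim of confirmed home safety with what the usability work can carry: for example, that a first version of the training app was tried by 30 older adults, with their ratings and any side effects reported. Make it consistent with the fall and cybersickness risks named under Challenges, Potential Risks and Challenges, and Limitations.

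**Cost.** One extra table from data that the article says were collected, and a less favourable safety statement. No change to the conduct of the trial is involved.

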### Dissemination

The study results will be published in scientific journals and presented at appropriate scientific conferences. All materials and papers will be written by the researchers. No services of external copywriters will be used. The study protocol was registered and published on ClinicalTrials.gov.

## Discussion

### Potential Benefits

VR-based interventions can significantly improve the quality of life for healthy older individuals in several ways. First, VR offers a means of mental stimulation and cognitive engagement. By immersing the user in various environments, tasks, and games, VR can delay cognitive decline by enhancing various cognitive abilities such as memory, attention, and problem-solving skills [42,43]. Second, VR interventions can be used to support physical activity and rehabilitation by providing a safe environment for older adults to improve their balance and flexibility and reduce the risk of falls and injuries [14]. Third, VR provides opportunities for social interaction and connectivity, thus combating the isolation and loneliness often experienced by older people. VR meetings and games can promote engagement with family and peers, and exploring VR worlds can offer a sense of adventure and travel without physical limitations [15]. Finally, VR apps can be used to manage anxiety and stress, promote general well-being, and provide leisure opportunities, thus positively impacting quality of life [44].

### Potential Risks and Challenges

Several potential risks and challenges are associated with using VR interventions in the older adult population, and these should be taken into consideration to maximize their benefits and minimize any potential harm. First, suboptimal and prolonged use may be associated with physical discomfort or cybersickness, comprising symptoms such as nausea, disorientation, or eyestrain [29]. Second, there can be a significant learning curve for older adults unfamiliar with the technology, and some individuals may find the technology intimidating or stressful, leading to rejection or noncompliance [45]. Third, if the person is unaware of their real-world surroundings while immersed in the VR environment, they may be at risk of falls or accidents. Finally, while the cost of VR hardware has decreased, it can still be expensive, especially for high-quality systems.

### Limitations

One limitation of this study is that it did not determine the degree of function of the participants by an appropriate objective tool; instead, it was evaluated by a research team based on a medical interview during the screening process. While this approach provided some insight into the participants’ functional independence in activities of daily living, it may have introduced subjectivity and potential bias. Objective tools, such as standardized assessments or performance-based measures, could have provided more reliable and valid measures of older adults’ functioning. For instance, widely recognized tools such as the Timed Up and Go (TUG) [46] test for mobility and the Instrumental Activities of Daily Living (IADL) scale [47] for more complex tasks could offer standardized and quantifiable metrics. Future studies should consider incorporating these objective tools to obtain a more comprehensive and accurate assessment of functional ability.

Another potential limitation of the study relates to the occurrence of cybersickness among participants engaging with VR interventions. Cybersickness, a condition characterized by symptoms such as dizziness, nausea, and headache, mirrors the symptoms of motion sickness but is induced by immersive VR environments. The incidence of cybersickness varies among individuals and can significantly impact the user’s ability to engage with VR-based interventions over time [29]. This limitation is particularly relevant as it may affect the participant’s adherence to the intervention, potentially skewing the study’s outcomes. Future research should aim to identify strategies to minimize cybersickness, possibly through the adaptation of VR content, the duration of sessions, or the inclusion of breaks, to enhance the comfort and participation of all users.

Furthermore, the study faced challenges associated with Wi-Fi connectivity, which represents another significant limitation. A reliable Wi-Fi connection is crucial for the seamless delivery of VR content and the uninterrupted participation of subjects in the study. Issues with Wi-Fi connectivity, such as signal instability or bandwidth limitations, can disrupt the VR experience, leading to fragmented sessions or the inability of participants to complete the intervention as planned. This technological constraint not only affects the consistency and quality of the intervention delivery but also potentially impacts the engagement and satisfaction of participants. Addressing Wi-Fi connectivity issues is essential for ensuring the fidelity of VR-based interventions, and future studies may need to consider alternative solutions or backup options to mitigate these challenges, ensuring a smooth and effective implementation of VR technology in research settings.

### Conclusions

Previous research found that VR therapy can improve the well-being of older adults in long-term care, rehabilitation hospitals, and older adult care residences, who often experience cognitive decline, reduced mobility, and isolation [22]. We intend to publish our findings in a future study, and we believe that they will provide further information on the effect of immersive VR therapy among healthy, community-dwelling older adults regarding their cognitive performance, tolerance, and technology acceptance. Even so, further research is needed to explore the long-term effects, optimal intervention designs, and specific populations that may benefit most from VR-based interventions.

## Appendix

Multimedia Appendix 1 Informed consent.

Multimedia Appendix 2 Music selection.

## Abbreviations

CNS-VS: Central Nervous System Vital Signs
CoSoPhy FX: Cognitive, Social, and Physical Effects
GAD-7: General Anxiety Disorder 7-item questionnaire
GDPR: General Data Protection Regulation
HMD: head-mounted display
IADL: Instrumental Activities of Daily Living
MoCA: Montreal Cognitive Assessment
MUL: Medical University of Lodz
TUG: Timed Up and Go
VR: virtual reality
WHO: World Health Organization
